### Intervention and compliance

Participants will be randomly allocated to either a probiotic or placebo supplement. The two supplements will look identical. The probiotic capsules will contain 3 × 10^9^ CFU of freeze-dried *Bifidobacteria* along with potato starch, magnesium stearate, and ascorbic acid as excipients. The placebo will contain only the excipients. Participants will keep the supplement at room temperature and will consume the intervention once a day with a meal for approximately 8 weeks. This is approximate to account for a few days’ variation in duration of individual menstrual cycles. Any adverse events that are believed to be due to the consumption of the probiotic will be assessed in daily questionnaires and reviewed by the study physician to assess unintended effects of the trial.

The study will be monitored monthly by the study sponsor through a data monitoring form. Study coordinators will monitor questionnaire completion daily to ensure participant compliance. If a participant does not complete a questionnaire, a study coordinator will contact them with a reminder. If the study coordinator notices that the participant did not consume their supplement, the participant will be contacted to remind them to consume their supplement. Compliance will be assessed by counting the number of study supplement capsules that were not consumed. Compliance is calculated by determining the number of capsules consumed divided by the number expected to have been taken to obtain the percentage consumed. In the daily questionnaire, participants will also be asked if they consumed the study supplement. In the event of a discrepancy between the information in the daily questionnaire and the amount of study supplement returned, compliance will be determined based on the product returned unless an explanation for loss of product has been provided. Participants found to have a compliance of < 80% will be considered noncompliant.

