## Methods and analysis

### Overall design

This 9-week randomized, double-blind, placebo-controlled clinical trial will be conducted online across the contiguous United States and at the University of Florida (i.e., exploratory subgroup providing biological samples), in accordance with the International Conference on Harmonizaiton-Good Clinical Practice (ICH-GCP) guidelines. This study observes a two-arm parallel design with a 1:1 allocation, including an exploratory subgroup providing fecal and vaginal swab samples. A diagram detailing the study flow is shown in Fig. 1. The protocol was prospectively registered on ClinicalTrials.gov; the database record (NCT04457401) will be updated to reflect any amendment to this protocol over the course of the study.

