### Randomization, sequence concealment, and blinding

This is a double-blind study; the sponsor representatives involved in the study, the investigators, the participants, and any health care professional or site personnel involved in participant management or outcome assessment will remain blinded. Participants will be stratified on their typical abdominal pain score at the beginning of the study and randomized to either the probiotic or placebo supplement in blocks of a pre-specified size. This abdominal pain score will reflect the first 3 days of their typical menstrual cycle and will be on a scale of 3 (mild discomfort) to 7 (very severe discomfort). To maintain a balance in numbers of participants in the main and subgroup studies, randomization will be conducted separately for the main and subgroup studies. Participants will be stratified into two groups including those with mild abdominal pain (score of 3) and those with moderate to very severe abdominal pain (scores 4–7).

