**Table 1 Tab1:**
[figure not shown]
Schedule of activities

^a^Study days may vary due to variability in menstrual cycle length

^b^Each cycle and its assessments will be based on the first day of menstruation (first day of bleeding)

^c^Probiotic or Placebo

Following consent and approximately 1 week before menstruation, participants will be asked to complete a pregnancy test and will begin completing daily questionnaires. Briefly, daily questionnaires will inquire about GI symptoms, abdominal pain as measured by the visual analog scale [36–40], duration of abdominal pain, stress, stool form, stool frequency, adverse events, and medications taken, including the dose and administration schedule. Study days 3, 28, and 56 will be referred to as “menstruation 1,” “menstruation 2,” and “menstruation 3,” respectively. On the third day of their menstrual cycle (day 3/menstruation 1), they will begin consuming their study supplement (start of intervention). On the days participants experience GI symptoms related to the menstrual cycle, they will answer an additional questionnaire, which is a modified daily version of the GSRS to access GI symptoms. Approximately 7 days prior to menstruation 1 (study day − 7) and 3 days after each menstrual event (study days 3 and 31), participants will answer the Menstrual Symptom Questionnaire to assess symptoms leading up to and during menstruation. Seven days after each menstrual event (study days 7, 35, and 59), participants will be administered the Perceived Stress Scale to assess stress levels over the previous month [41]. Participants will also answer two validated weekly questionnaires including the GSRS and the Digestion-associated Quality of Life Questionnaire each week they are in the study. Each participant will also complete a 24-h dietary recall assessment at four points during the study (study days − 7, 21, 28, and 35) throughout the menstrual cycle. Finally, participants will also complete the Food Cravings Inventory (FCI) during the first and second menstrual event (study days 1 and 28). Participants will complete all questionnaires online using their assigned study number to maintain confidentiality. Questionnaires will be administered via Qualtrics Survey Software (Qualtrics Software Company) and data will be maintained on password-protected, encrypted computers.

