#### Data monitoring

The study personnel will download and monitor data weekly to inspect for errors and compliance. The study personnel will also send a study monitoring report monthly to the study sponsor that includes information on the status of the trial, including adverse events. The study sponsor will have one data monitoring visit throughout the study.

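### Assessment and physician review of adverse events depend on a belief that the probiotic caused them, while the daily questionnaire and sponsor report carry no such limit

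*Protocol article*

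**What the plan says.** Three sections of the protocol article describe how adverse events are handled.

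- **Intervention and compliance**: "Any adverse events that are believed to be due to the consumption of the probiotic will be assessed in daily questionnaires". The same sentence continues that these events are "reviewed by the study physician to assess unintended effects of the trial". It does not say who forms the belief.
- **Study conduct** (text after Table 1): the daily questionnaires ask, among other items, about "stool frequency, adverse events, and medications taken, including the dose and administration schedule". No condition on cause is attached.
- **Data monitoring**: the monthly report to the sponsor "includes information on the status of the trial, including adverse events". Again there is no condition.

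Two design features bear on this. Overall design describes a "two-arm parallel design with a 1:1 allocation". The blinding section covers sponsor representatives, investigators and participants, and adds that "any health care professional or site personnel involved in participant management or outcome assessment will remain blinded".

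**The concern.** The first sentence makes presumed cause the entry condition for assessment and medical review. That is awkward in this trial for three reasons.

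- Nobody who might form the belief knows the allocation, so it is a guess. Read literally, an event on placebo can never be due to the probiotic, so the rule leaves unclear how events in half the participants are handled.
- The stated purpose of the review is to find unintended effects, yet events are screened on presumed cause before the physician sees them.
- The women are enrolled because they usually have abdominal pain in the first days of menstruation, and the Introduction lists headache, bloating, diarrhea and constipation as ordinary menstrual symptoms. A product effect of that kind has a ready alternative explanation and could fail the condition.

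At stake is whether an event that nobody attributes to the supplement is looked at by a physician. A coordinator working from this text could not tell whether to forward every reported event or only the suspected ones.

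**Working it through.** **Passages side by side.** Each step in the handling of adverse events has this scope:

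- Collection in the daily questionnaire: no limit in Study conduct; limited to events believed due to the probiotic in Intervention and compliance. Both sections refer to daily questionnaires, so they conflict.
- Physician review: limited. Intervention and compliance is the only place that describes it, and nothing elsewhere widens it.
- Monthly report to the sponsor: no limit.
- Comparison between arms: none stated. Adverse events are not among the outcomes under Study outcomes, and Statistical analysis does not mention them.

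The clear restriction is therefore on physician review. The scope of collection is contradictory, and sponsor reporting is unrestricted.

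**Inputs for an illustration.** The article gives no figure for adverse events. The only planned number used is 93 per arm, and it reproduces: with a difference of 9, an SD of 19.99, two-sided alpha 0.05 and 80% power, n = 2 × (1.96 + 0.842)² × 19.99² / 9² = 77.4, so 78 by the normal formula; the t-test version gives 78.4, so 79, as stated. Then 79 / 0.85 = 92.9, so 93. The event rates and the shares passing the filter below are assumptions, not taken from the document.

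**Formula.** If a share s of events passes the filter, the observed rate is p × s. With observed rates a and b, mean m and n per arm, approximate power is Φ[(|b − a| − 1.96 × SE0) / SE1], where SE0 = √(2m(1 − m)/n) and SE1 = √((a(1 − a) + b(1 − b))/n).

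**Same filter in both arms, true rates 10% and 20%.**

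- All events pass: SE0 = 0.0524, SE1 = 0.0519, so Φ[(0.10 − 0.1026)/0.0519] = Φ(−0.05), about 48%.
- Half pass in each arm: the observed rates are 5% and 10%. SE0 = 0.0386, SE1 = 0.0385, so Φ[(0.05 − 0.0757)/0.0385] = Φ(−0.67), about 25%.
- The risk difference halves from 10 to 5 points. The risk ratio stays at 2.0.

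**Same filter, equal true rates of 20%.** Half pass in each arm: 10% against 10%. No false difference arises.

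**Different filter by arm, equal true rates of 20%.** If 30% pass on placebo and 50% on probiotic, the observed rates are 6% and 10%: a difference of 4 points and a risk ratio of 1.67 where none exists. This needs attribution to be related to allocation.

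**The case against.** The strongest reply is that this is one loosely worded sentence. It does not say that other events go unrecorded, and two sections describe adverse events with no limit. The unblinding provision under Sequence generation covers the codes of both supplements, so events on placebo are plainly foreseen. Abdominal pain, GI symptoms, and stool form and frequency are collected daily in all women, and the GSRS weekly, without attribution to the product (only the additional modified daily GSRS is tied to days with menstrual symptoms). They are analysed as outcomes by intention to treat. The article also condenses a fuller protocol, where review procedures may be set out.

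Much of this stands, and it rules out two stronger readings that a reader might draw.

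- *Adverse events are collected only if attributed to the probiotic.* The documents do not support this: Study conduct and Data monitoring carry no such limit.
- *The comparison of adverse events between arms is biased.* No such comparison is stated, and under intact blinding the filter acts alike in both arms. Attribution could become related to allocation, for instance through correct guesses about the supplement or after a code is unblinded, but nothing in the document shows that it would.

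The daily outcomes also mean that an effect on average pain or stool pattern would not vanish from the data. They do not replace medical review of an individual event, and they do not cover every kind of event. Nor does the condensed format dispose of the point: the article does not leave the scope of review open but states a rule for it, and that rule conflicts with the other sections.

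**Conclusion.** The point holds as an inconsistency and a badly drawn rule for medical review. Intervention and compliance limits assessment and physician review to events believed to be due to the probiotic; Study conduct and Data monitoring do not. Under blinding the belief is a guess, and the status of events on placebo is unclear. If the sentence is followed, events put down to another cause can go without medical review. The expected effect is under-counting, and so lost sensitivity to harm, in both arms. A distorted arm contrast would require attribution to depend on allocation.

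The size cannot be derived from the document. The fall in power from about 48% to 25% rests on assumed rates of 10% and 20%, an assumed share of one half in each arm and 93 women per arm; it shows the direction and order of the loss, not an estimate. The primary outcome, the sample size and the stated analyses are unaffected. The conclusion does not rely on the article's general commitment to ICH-GCP; the conflict between its own sections is enough.

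**What to change.** Reword the sentence under Intervention and compliance to agree with Study conduct and Data monitoring: all adverse events in both arms are recorded in the daily questionnaires whatever their presumed cause, all are reviewed by the study physician under blinding, and causality is judged afterwards as a separate item. Refer to the study supplement rather than to the probiotic, so that the rule applies equally to placebo.

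The cost is wording plus a few more events for the physician to read, since the daily questionnaire is already described as asking about adverse events. The Trial registration entry says that the trial was completed in December 2021. If data collection is over, the final report should state which rule was followed for recording and for review.

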### Study outcomes

The primary outcome is the change in abdominal pain intensity related to the menstrual cycle at the beginning of the menstruation, calculated as the average of the first 3 days of “menstruation 2” when on the intervention minus the average of the first 3 days of “menstruation 1” prior to initiating the intervention. A daily visual analog score will be used to measure abdominal pain intensity between women on the probiotic versus the placebo interventions. We hypothesize that women consuming a probiotic will experience a greater decrease in abdominal pain compared to women on the placebo.

The secondary outcomes are defined as follows:To determine the effect of the probiotic on the number of days with abdominal pain (score above 0), assessed by the daily visual analog scale. We hypothesize that women who consume the probiotic will experience a decrease in the number of days with abdominal pain.To determine the effect of the probiotic on GI symptoms throughout the menstrual cycle, as measured by a daily modified version of the GSRS. We hypothesize that women who consume the probiotic will experience a decrease in the severity of GI symptoms compared to women who consume a placebo.To determine the effect of the probiotic on menstrual symptoms, as measured by the Menstrual Symptom Questionnaire. We hypothesize that women who consume the probiotic will experience decreased menstrual symptoms compared to women who consume a placebo.To determine the effect of the probiotic on stress, as measured by daily self-reported stress and a monthly Perceived Stress Scale. We hypothesize that women who consume the probiotic will experience decreased levels of stress compared to women who consume a placebo.To determine the effect of the probiotic on stool form and frequency throughout the menstrual cycle, as measured by the Bristol Stool Form Scale. We hypothesize that women who consume the probiotic will experience a more ideal consistency and pattern of bowel habits compared to women who consume a placebo.To determine the effect of the probiotic of digestion-associated quality of life, as measured by Digestion-Associated Quality of Life Questionnaire. We hypothesize that women who consume the probiotic will experience a better quality of life compared to women who consume the placebo.To determine the effect of the probiotic on dietary intake, as measured by the Automated Self-Administered 24-hour (ASA-24). We hypothesize that energy intake will not be different between the probiotic and placebo groups.To determine the effect of the probiotic on food cravings, a measured by the Food Craving Inventory (FCI). We hypothesize that women who consume the probiotic may experience fewer cravings than women on placebo.To explore the effect of the probiotic on the gut and vaginal microbiota in a subgroup of the study population. Recovery of the probiotic in the stool and vaginal samples will be assessed. Changes in the concentrations of the probiotic will be measured with specific DNA (or antibodies) in fecal and vaginal samples (e.g., qPCR, flow cytometry, or other methods). Effects of the probiotic interventions on overall microbiota composition (e.g., Illumina 16S rRNA sequencing) will also be measured. We hypothesize that women who consume the probiotic may show changes in microbiota composition compared to women on placebo.

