While we will encourage participants to avoid pain relievers, consumption of over the counter pain relievers to assist with the pain associated with the menstrual cycle will be allowed for ethical reasons. We will ask participants to report any pain reliever consumption and instruct them to report their greatest abdominal pain intensity prior to consumption.

A subgroup of 20 participants per arm will also be asked to sign a separate informed consent form which will detail all of the main study tasks and will also include information on providing ten stool and vaginal swab samples during the study (study days − 7, 1, 7, 14, 21, 28, 35, 42, 49, and 56). These participants will be provided with stool and vaginal swab collection kits and receive instructions on how to self-collect these samples at home. Participants will be asked to return the samples to the study site. This subgroup will also complete additional 24-h dietary recalls (study days 1, 42, 49, and 56).

Participants will continue to answer daily questionnaires until the third day of their third menstrual cycle, at which point they will discontinue answering questionnaires and consuming the study supplement. At the conclusion of the study, blinding efficacy will be assessed via a questionnaire asking participants which supplement they thought they were consuming. Participants will be instructed to either return any unused capsules or text a picture of the remaining capsules to the study coordinator for compliance assessment.

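### The exploratory microbiota comparison uses the overall 16S profile, so in stool the capsule organism's own reads can create a between-arm difference

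*Protocol article*

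**What the plan says.** The last secondary item under Study outcomes in the protocol article sets out three things for the subgroup.

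- Recovery: "Recovery of the probiotic in the stool and vaginal samples will be assessed".
- Quantity of the product: "Changes in the concentrations of the probiotic will be measured with specific DNA (or antibodies) in fecal and vaginal samples".
- Composition: "Effects of the probiotic interventions on overall microbiota composition (e.g., Illumina 16S rRNA sequencing) will also be measured".

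The hypothesis attached to the item is: "We hypothesize that women who consume the probiotic may show changes in microbiota composition compared to women on placebo". It has no direction and no restriction to the organisms that were there before dosing.

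Intervention and compliance gives the contrast between arms. The active capsule holds 3 × 10^9 "CFU of freeze-dried *Bifidobacteria* along with potato starch, magnesium stearate, and ascorbic acid as excipients", taken daily for about 8 weeks. For the other arm: "The placebo will contain only the excipients".

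Study conduct gives the timing. Supplementation starts on day 3. The subgroup of 20 per arm provides stool and vaginal swabs on days −7, 1, 7, 14, 21, 28, 35, 42, 49 and 56. Daily reporting runs to the third day of the third menstrual cycle, "at which point they will discontinue answering questionnaires and consuming the study supplement". No sample is scheduled after that. The Abstract and Objectives call this part exploratory.

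**The concern.** The item already asks whether the product can be recovered, with an organism-specific assay. The composition comparison is presumably there to add something: whether the community differs beyond the presence of what was swallowed. A 16S profile of the whole sample does not make that separation. Reads from the dosed organism enter the profile in one arm only, and they raise that arm's share of one taxon even if no resident organism has changed. Because no sample falls after dosing stops, timing cannot separate transit from a change in the community either.

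What is at stake is interpretation. A positive composition result could be read as a biological effect on the gut community when it shows only that women took their capsules.

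**Working it through.** **No figure to reproduce.** The article's only calculation is the sample size for the pain outcome. It plays no part here.

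**Timing.** Dosing starts on day 3, so days −7 and 1 are before dosing. The other 8 of the 10 samples (days 7 to 56) fall during it, and none comes after.

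**Assumed read share.** The documents give the daily dose (3 × 10^9 CFU) but no share of stool reads. Assume full passage and a daily stool load L of 10^11 to 2 × 10^13 bacteria. The share is 3 × 10^9 / (L + 3 × 10^9):

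- L = 10^11: 3 × 10^9 / 1.03 × 10^11 = 2.9%
- L = 10^12: 0.30%
- L = 10^13: 0.03%
- L = 2 × 10^13: 0.015%

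**Model A: whole-community tests.** There are 20 women per arm, both arms drawn from the same resident community (150 taxa, Dirichlet variation, resident Bifidobacterium about 3%) and 20,000 reads per sample. One product taxon, absent from all placebo women, is added to the active arm at share f. There are 150 runs per f, so Monte Carlo error near 5% is about √(0.05 × 0.95 / 150) = 1.8 percentage points. Percentage of runs significant at 0.05:

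| Test | f = 0 | 0.03% | 0.3% | 3% |
|---|---|---|---|---|
| Bray-Curtis (abundance-weighted) | 4 | 7 | 11 | 100 |
| Genus Bifidobacterium, rank test | 7 | 5 | 6 | 99 |
| Jaccard (presence/absence) | 2 | 100 | 100 | 100 |
| Product taxon, rank test | 0 | 100 | 100 | 100 |
| Bray-Curtis, product removed and rescaled | 3 | 4 | 6 | 5 |
| Jaccard, product removed and rescaled | 3 | 6 | 6 | 4 |

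The last two rows show that the remedy brings rejection back to about the nominal 5%. At f = 10% and 20% these two tests also stay between 2% and 7%.

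**Model B: genus-level change.** A two-sample t test on change in log10 genus share, 20 per arm, between-woman SD 0.7. The capsule share a enters as resident share × (1 − a) + a. Percentage of trials significant with no resident effect:

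| Capsule share a | Resident median 1%, change SD 0.4 | Resident median 5%, change SD 0.6 |
|---|---|---|
| 0 | 5 | 5 |
| 0.1% | about 15 | 5 to 6 |
| 0.3% | about 45 | about 9 |
| 1% | about 91 | about 23 |
| 3% | over 99 | about 59 |

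At a = 0.3%, over resident medians of 5% down to 0.3% and change SDs of 0.4 to 0.6, rejection runs from about 9% to 91%. The genus-level result is therefore governed by values that the documents do not give.

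**The case against.** The article fixes no metric, taxonomic level or decision rule. Read filtering and the choice of distance are details that a condensed article may leave to a fuller plan. This stands: no flawed test has been prespecified, and the absence of pipeline detail is no fault. What remains is that the hypothesis itself, which the article does state, is set on the overall profile, so a plan faithful to it would test the full profile.

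It can also be said that a swallowed organism found in stool is part of the composition, that the article nowhere claims a resident-community effect, and that recovery will be reported beside it. All true. The wording is not an error. It leaves one result open to two explanations that the same data could separate.

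The magnitudes are assumption-driven, and this stands too. The Jaccard and product-taxon figures of 100% require that no placebo woman carries a matching sequence, which may fail if 16S cannot tell the product from resident bifidobacteria.

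A reader might infer more than the documents support:

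- That a positive composition result would have to be an artefact. At low read shares, abundance-weighted and genus-level tests can be little affected.
- That the vaginal comparison is equally exposed. Nothing in the documents quantifies transfer from an oral capsule to vaginal swabs, and every calculation here concerns stool.
- That all samples are contaminated by dosing. Days −7 and 1 precede it.
- That any statement about composition should rest only on the profile without the product. Where the whole genus has to be removed, that profile loses real change in resident bifidobacteria, a group that the Introduction links to health.

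**Conclusion.** The point holds as a matter of interpretation. As stated, the stool composition comparison can be met by the capsule organism's own reads with no effect on the resident community, and to that extent it repeats the recovery measurement. How likely this is depends on the metric and on an unstated read share. Taxon-level and presence/absence measures are the most exposed. Abundance-weighted distances move little below about 0.3% and are fully affected at about 3% in the model used. Genus-level tests range from almost unaffected to badly inflated, according to the assumed resident abundance and variability. The item is exploratory with 20 per arm, and no primary or clinical secondary result or sample size depends on it. This is a cheap improvement, not a defect in the trial.

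**What to change.** In the microbiota item under Study outcomes, state that the between-arm comparison of composition and diversity will be reported twice: on the full profile, and after removing reads assigned to the dosed organism and rescaling the remainder. Where 16S cannot separate the product from resident bifidobacteria, remove the genus Bifidobacterium as a sensitivity analysis. Report recovery separately, and claim an effect on the resident community only if it is seen without the dosed organism's reads.

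The cost is one further pass through the same sequence data, with no new samples. Where the whole genus is removed, that analysis cannot show change in resident bifidobacteria, which is why the full-profile result stays alongside it.
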